Examine the association between SMI and weight change.Examine the association between SMI and change in cardio-metabolic risk factors for CVD.Examine the association between SMI and incidence of and mortality from CVD.Compare incidence of advice and offer and actual referral to weight management services in people with both SMIs and BMI ≥25 kg/m^2^ with controls.

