#### Study cohort

We will select a study cohort from the CPRD Aurum to investigate objectives 1–3. We will identify and extract the records in the primary care and HES dataset for all patients with a diagnosis of SMI (hereafter *exposed*) and who are eligible for data linkage. Diagnostic Read codes, which are the standard clinical codes used in UK general practice, will be used to identify an SMI diagnosis. We will also use codes according to the International Classification of Diseases version 10 (ICD-10) from the HES data. The date of the first SMI Read code will be used as the index date, which is the earliest date that an exposed patient may enter the study. From the study cohort, a subcohort of patients will be selected to investigate objective 4. To enter the subcohort, the exposed patient needs a recorded BMI ≥25 kg/m^2^ at any time after the index date. All information will be extracted for the period 01 January 1998 to 31 October 2020—the earliest and latest dates respectively that data are available.

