#### Comparison group

The unexposed represents the counterfactual and will include patients without an SMI Read code ever (hereafter *unexposed*) drawn from the source population. Up to four unexposed matches will be selected at baseline only if they have a qualifying weight Read code within±one year of the index date to the exposed in which they are matched. The matching variables include: age, sex, practice and calendar time. All weight Read codes will be extracted.

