### Confounding

We have identified confounding variables using directed acyclic graphs (DAGs), which aims to theoretically formalise potential confounders, colliders and biasing relationships.^26^ The DAG for each objective is described in online supplemental material S1. The DAG for objective 1 shows one direct path from the exposure (ie, SMI) to the outcome (ie, weight change), and four indirect paths: via health behaviours (ie, alcohol use, smoking and diet), SES status, psychotropic medication, and healthcare access and provision. Diet and physical activity are latent variables in CPRD Aurum because they are unmeasured. There are three confounding paths: via age, sex and ethnicity.^27 28^ Thus, the minimally sufficient adjustment for the total effect of SMI status on weight is to adjust for age, sex, and ethnicity.

10.1136/bmjopen-2021-053427.supp1Supplementary data

Frequency matching will ensure our ability to adjust for confounding variables that include age, sex, and calendar year, and matching on practice will remove practice-specific variables. In addition, we will fully adjust our models by considering several covariates in the relationship between the exposure and outcome (see table 2). All categorical variables will be analysed using the natural reference category as the reference group. Data on individual prescriptions for psychotropic and cardio-metabolic medications will be extracted from the primary care data from index date until censoring. For psychotropic medications, drugs will be classified according to the British National Formulary. For objectives 2 and 3, we will assess the impact of weight gain on change in cardio-metabolic risk factors and incidence of CVD using mediation analysis to allow us to estimate the direct (unmediated) and indirect (mediated) effects of SMI on CVD risk and incidence. To do this, we will fit two regression models: one regressing the outcome on the exposure, adjusting for confounders and another regressing the mediator on the exposure and confounders using the Stata *Med4way* command to estimate mediated effects.^29^ For objective 4, we will assess the presence of confounding by comparing estimates with and without adjustment. We will use Read codes, which have been previously developed by our team, to identify outcome and covariate records.

**Table 2 T2:** Confounders

Confounders and covariates		Measures

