Health behaviours	Smoking status	Categorical (0=never; 1=ex-smoker; 2=current smoker (light: 1–9 cigarettes/day; moderate: 10–19 cigarettes/day; heavy: 20+ cigarettes/day)). This is coded in GP records. We will use the most recent recorded value of smoking status at the study start date.
	Alcohol use	Continuous (units per week). This is coded in GP records. We will use the most recent recorded value of alcohol use at the study start date.
Demographics	Socioeconomic status (SES)*	Categorical (quintiles)
	Ethnicity†	Categorical (white; Asian or Asian British; black or black British; other ethnic group, mixed)
	Sex†	Binary (0=male; 1=female)
	Age at study entry, in years	Continuous
Physical and/or medical factors	Baseline weight status (body mass index (BMI))	Categorical (normal weight (BMI 18.5–24.9 kg/m^2^); overweight (25.0–29.9); obese (30.0–34.9); severe obesity (35.0–35.9); morbid obesity (40.0–44.9)
	Psychotropic medication	Categorical (antipsychotics (first-generation and second-generation); antidepressants; mood stabilisers)
	Cardio-metabolic medication	Categorical (blood glucose lowering medications; antihypertensive treatments, statins)
We include the following additional variables for objectives 3 and 4 only		
CVD risk factors	Total cholesterol/HDL ratio	Continuous
	Systolic and diastolic blood pressure	Continuous
	Glycaemia	HbA1c/fasting blood glucose (FBG)

*This variable is grouped according to practice level Index of Multiple Deprivation. This is an indicator of material deprivation based on income; employment; health deprivation and disability; education, skills and training; crime; barriers to housing and services; and living environment. It is categorised as quintiles 1–5 with 1 being the most deprived and 5 being the least deprived.

†This variable is grouped according to recommendations by the UK Office for National Statistics.^33 34^

CVD, cardiovascular disease; GP, general practitioner; HbA1c, haemoglobin A1c; HDL, high-density lipoprotein.

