### Statistical analysis

Analyses will be conducted in Stata using an estimation approach. We do not intend to impute missing data. The entry date into the analysis is the index date. The outcome date is the earliest of: (1) the date of death or (2) date of diagnosis of the outcome of interest. For objectives 1 and 2, we will use all repeated measures and run separate models for each analyses. For objective 3, we will use the first recorded diagnosis of the outcome of interest rather than recurrent events. Patients who do not have the outcome of interest will be censored at the earliest of: (1) date of death, (2) date of leaving the practice, (3) date of the latest download of data or (4) the study end date.

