#### Primary analyses

For objectives 1 and 2, the outcome will be visually inspected by plotting trajectories of weight and cardio-metabolic risk factor change using all repeated measurements for patients with SMI versus patients without SMI. For these analyses, we will use a mixed-effects linear regression model including terms for SMI, time and their interaction to estimate regression coefficients with 95% CIs by SMI status. Models incorporating psychotropic medications will analogously include medication-time multiplicative interaction terms. We will include a random effect for individual and practice identifier to account for intra-class correlation resulting from common practice membership. Diagnostic tests will be conducted to confirm linear regression assumptions are met including linearity of residuals, residual normality using quantile–quantile (Q–Q) plots, and residual heteroscedasticity using residual versus fitted value plots. We will assess for exploratory subgroup effects by adding interactions (eg, by age, sex, ethnicity and SES) and, if significant, we will assess the strength of the associations in separate subgroups for clarity. For objective 2, we will model the association between weight and cardio-metabolic change using restricted cubic splines to allow for non-linear associations. For objective 3, we will use Kaplan-Meier survival estimates for the exposed and unexposed groups to estimate the distribution of time from index date to total and fatal CVD and mortality (all-cause). The statistical equivalence of the two curves will be examined using the log-rank test. This analysis will use a survival from index date between the exposed and unexposed groups using an adjusted Cox proportional hazards regression model with follow-up time as the timescale. Restricted cubic splines will be computed with five knots to visually explore non-linear associations between the exposure and the outcomes. For objective 4, we will use a Poisson regression examining person-time to estimate the rate at which patients who received weight management services over the study period in patients with SMI compared with patients who do not have SMI, adjusting for confounders and BMI.

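### Objective 4 appears to adjust for BMI at baseline, although entry and referral depend on later BMI; if SMI patients gain more weight, under-referral at equal BMI can be partly or wholly hidden

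*Protocol article*

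**What the plan says.** - **Model.** Under Primary analyses, objective 4 uses Poisson regression on person-time to compare rates "in patients with SMI compared with patients who do not have SMI, adjusting for confounders and BMI". No timing is given for BMI.
- **BMI covariate.** Table 2 (Confounding) has one BMI row, which begins "Baseline weight status (body mass index (BMI" and is divided into bands starting at normal weight. The text before the table adds: "All categorical variables will be analysed using the natural reference category as the reference group". Table 2 covers objective 4 expressly: it lists extra variables for objectives 3 and 4 (lipid ratio, blood pressure, glycaemia), and an updated BMI is not among them.
- **Entry to the subcohort.** Under Study cohort, "the exposed patient needs a recorded BMI ≥25 kg/m^2^ at any time after the index date".
- **Clock.** Under Statistical analysis, "The entry date into the analysis is the index date". Follow-up can last up to 22 years (Duration of follow-up).
- **Controls.** They are matched "only if they have a qualifying weight Read code within±one year of the index date". The objective itself makes the comparison "in people with both SMIs and BMI ≥25 kg/m^2^ with controls". No BMI rule for controls is stated.
- **Referral and BMI.** The Introduction describes advice or referral as the first-line step for people with a BMI above 25.

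**The concern.** The BMI in the model, read from Table 2, is neither the BMI that made the patient eligible nor the BMI the GP sees when deciding on referral. A patient of normal weight at the index date whose BMI reaches 31 three years later enters a subcohort defined by BMI of at least 25, yet is adjusted as normal weight, the natural reference category.

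The mismatch need not be equal in the two groups. The Introduction discusses excess weight gain in people with SMI and the rapid gain linked to psychotropic drugs, and objective 1 studies weight change as a consequence of SMI. If that expectation is right, SMI patients in a given baseline band are heavier than their controls by the time referral is considered. Their greater need raises their referral rate, and the model credits this to SMI status.

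The Discussion says the results should show whether people with SMI are being offered support with their weight. The costly error is therefore false reassurance: less frequent referral at a given BMI could look like equal care.

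**Working it through.** **What there is to reproduce.** The article gives no figure for objective 4. Its sample size of 3907 concerns CVD incidence and has no bearing here. The size of the shift has to be illustrated.

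**Inputs from the article.** Referral rate 20.0 per 1000 person-years (Introduction); mean follow-up 4.6 years and one exposed to four unexposed (Sample size calculation).

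**Assumptions, none of them in the article.** True SMI rate ratio at equal current BMI 0.80; index BMI with mean 27 and SD 5 kg/m²; SMI patients gain 1, 2 or 3 kg/m² more than controls; the referral rate rises 5% or 10% per kg/m².

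**Benchmark by hand.** If SMI patients carried the full extra gain g throughout, and referral rose smoothly by a fraction b per kg/m², the ratio within a baseline band would be 0.80 × (1 + b)^g:

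- b = 0.05: 0.80 × 1.05 = 0.84; 0.80 × 1.05² = 0.88; 0.80 × 1.05³ = 0.93.
- b = 0.10: 0.80 × 1.10 = 0.88; 0.80 × 1.10² = 0.97; 0.80 × 1.10³ = 1.06.

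Real gain builds up over time, so part of the person-time carries less than the full difference.

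**Simulation A.** Both groups enter at the first BMI of at least 25, and the extra gain accrues over two years. The Poisson model contains SMI and baseline BMI band.

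**Simulation B.** Expected counts. The clock starts at the index date, as written; the gain is linear over 4.6 years (controls 0.3 kg/m², SD 1.5); there is no referral below BMI 25. It was run with the same BMI rule for controls and with no rule.

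Fitted rate ratio when the true value is 0.80:

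| Gradient per kg/m² | Extra gain (kg/m²) | A: both enter at BMI ≥25 | B: same BMI rule | B: no rule for controls |
|---|---|---|---|---|
| 5% | 0 | – | 0.80 | 0.82 |
| 5% | 1 | 0.83 | 0.83 | 0.88 |
| 5% | 2 | 0.86 | 0.86 | 0.93 |
| 5% | 3 | 0.90 | 0.88 | 0.98 |
| 10% | 0 | – | 0.80 | 0.82 |
| 10% | 1 | 0.86 | 0.85 | 0.89 |
| 10% | 2 | 0.93 | 0.90 | 0.96 |
| 10% | 3 | 0.99 | 0.95 | 1.02 |

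With BMI updated over follow-up, the estimate is 0.80 to 0.81 in every setting.

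A further simulation over the same range of gains and gradients gave 0.84 to 0.99 with both groups entering at the first BMI of at least 25, 0.85 to 1.01 with the clock at the index date, and 0.80 with current BMI.

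**Reading the results.** The shift comes from the extra weight gain: with none, and the same BMI rule in both groups, the baseline model returns 0.80. Simulation A already applies a common BMI rule and a common starting point, and the shift remains. Aligning eligibility and the clock would therefore not remove it.

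**The case against.** **The timing is inferred.** The model sentence names BMI apart from the confounders, although Table 2 already lists a BMI row among them, so another BMI variable may be meant. A condensed article can also leave such detail to a fuller document. This stands in part: a reader might infer that the article explicitly specifies baseline BMI in the objective 4 model, and it does not. But the baseline band is the only BMI covariate defined, in a table that covers objective 4, and repeated measures are mentioned only for objectives 1 and 2. If current BMI is meant, Table 2 needs correcting.

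**Current BMI lies on the path from SMI.** Adjusting for it removes part of any total effect, so a baseline-BMI model could be defended as a total-effect contrast, and objective 4 does not say it compares people at equal need. The first part stands. A reader might infer that the updated model is simply correct and the baseline model an error; the article does not support that, because it leaves the estimand unstated. Yet the baseline model is not a clean total-effect contrast either, since exposed patients are already selected on BMI recorded after the index date.

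**The direction is not established.** The Introduction itself calls the long-term effects of psychotropic drugs after diagnosis unclear, and objective 1 is there to measure weight change. This stands, and the conclusion is conditional on greater gain.

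**The simulations build in their answer.** Referral is generated from current BMI, so a current-BMI model must recover 0.80. True; they illustrate the size of the shift and do not prove that referral works this way.

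**Ineligible person-time pulls the other way.** Time between the index date and the qualifying BMI lowers the SMI rate. Simulation B includes that time, and the net shift was still upward whenever SMI patients gained more.

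**Updated BMI has measurement problems.** People with SMI have an annual review, and the Discussion expects more regular testing in overweight and obesity. Recording may therefore differ by group. This stands as a limit to report.

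**Conclusion.** The point holds conditionally. As written, the plan's only defined BMI adjustment is a baseline band, in a subcohort whose exposed members qualify on BMI "at any time after the index date". If SMI patients gain more weight than controls, the rate ratio moves upward relative to the comparison at equal current BMI. With the same BMI rule in both groups, a true 0.80 becomes about 0.83 to 0.99 under the assumed gains and gradients. At the 5% gradient it stays at or below about 0.90 in the tabulated runs, so under-referral is diluted but still visible. At 10% and 3 kg/m² it can disappear. With no extra gain there is no bias.

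A reader might infer that the ratio will be pushed above 1. That is not supported: values just above 1 (1.01 and 1.02) arise only at the extremes of the assumed range, 1.02 when controls face no BMI rule at all, which is a separate matter. The gain, the gradient and the BMI distribution are not in the article, so the size is illustrative. The estimand should be stated and both models reported.

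**What to change.** 1. State that the objective 4 contrast is referral at equal current BMI.
2. Fit the Poisson model with person-time split at each BMI record in both groups, entering the latest BMI before each interval as a continuous (spline) term.
3. Report the baseline-BMI model beside it, labelled as the contrast that leaves post-diagnosis weight gain unadjusted.
4. Report the limits: current BMI is partly a consequence of SMI, and a BMI value is carried forward for different lengths of time if recording frequency differs by SMI status. The number of BMI records per person-year and the age of the carried-forward value, by group, would show how far this matters.

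The cost is one added model specification and some descriptive output. All weight codes are already to be extracted (Comparison group), and BMI change is already an objective 1 outcome (Table 1), so no new data are needed.

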#### Sensitivity and secondary analyses

If necessary, data on missing confounders and covariates will be addressed by adjusting for missingness as a category. Sensitivity analyses will examine the impact of running the analyses with everyone included as discussed above and confined only to those with complete data. A second sensitivity analysis will be performed excluding patients that experience the outcome within 2 years of the SMI Read code to avoid reversed causality from other underlying disease.

## Ethics and dissemination

This study has been approved by the Independent Scientific Advisory Committee (ISAC) to the Medicines and Healthcare Products Regulatory Agency (reference: 20_000186). To guarantee the confidentiality of patient information, only the authors will have access to the data during the study. The full statistical code will be available from the authors after the publication of the results. The results of this study will be presented at scientific conferences and published in peer-reviewed journals.

## Discussion

In the UK, the NHS Long Term Plan commits the health service to greater action on reducing inequalities for the most overlooked groups. This study responds to this national agenda by focusing on the major cause of death for people with SMI—cardiovascular disease. We plan to leverage the power of a large UK primary care database to provide new insight on how these actions may be achieved.

Our results will estimate weight change, its risk factors including psychotropic medication, and its management in primary care as a preventative target for CVD. This could inform medication choice for people with SMI and clinicians, particularly if there are meaningful differences between drugs. In addition, our results will estimate the change in cardio-metabolic factors in people with SMI relative to those without SMI. This will be valuable to policy-makers because these are key risk factors for CVD that are being addressed through the NHS Long Term Plan. Furthermore, identifying the factors underlying the higher incidence of CVD will help us understand the degree to which these factors are valuable therapeutic targets. Lastly, understanding whether people with SMI are being offered support to manage their weight will inform national initiatives to overcome therapeutic nihilism. It is also important to understand whether there are differences in response between people with SMI and the general population, which would inform us about whether interventions need to be tailored to people with SMI for more personalised care. Ultimately, the results will offer a foundation to assess the degree to which the current focus on CVD prevention in people with SMI is having clinical benefits.

Since this study is observational, there are inherent strengths and limitations that are discussed. A strength of the study is its use of a representative, validated and sizeable dataset. Furthermore, the CPRD Aurum is an appropriate data source using primary care records. This will minimise selection, recall and respondent bias since UK general practices tend to have good levels of accuracy in recording prescriptions and clinical diagnoses. The results will also have direct and important applications to international guidelines on patient healthcare management, as well as to British primary care physicians, mental health services and members of the public with experience of SMI to initiate individual action. Finally, the longitudinal design is useful in addressing important clinical questions not usually possible within RCTs, and a matched-cohort improves efficiency since we will not need to include all controls, while tackling confounding.

Since the study is descriptive, any association observed would not imply an SMI diagnosis is causative of adverse physical health outcomes. However, we might assume the greater the magnitude of the observed association the less likely it is due to bias and more likely due to a causal process.^32^ Furthermore, diet and physical activity are unmeasured confounders because they are unobserved in CPRD Aurum. Similarly, other unmeasured confounders like poverty may place people with SMI at increased risk of homelessness, which has consequences on healthcare access and provision. We address this potential confounding by linking to patient level IMD as a proxy measure of SES, but acknowledge this may not fully capture deprivation and leaves room for residual confounding. Moreover, information bias may be present since the CPRD Aurum relies on a GP recording of health outcomes. Furthermore, we can only examine primary care prescriptions. Any prescribing solely within secondary care may not be included as this was not historically routinely recorded in GP records. Thus, it is possible we will miss the first prescription(s). Finally, physical health checks are not always performed on random samples of the population, and it is possible that more regular testing is done on people with overweight and obesity. We expect that some patients will have incomplete information recorded. However, by determining what proportion of patients do not have appropriate information recorded, we can evaluate the scale of these problems, and highlight the need for improved recording for continuity of care between healthcare professionals.
